**Figure 1. F1:**
[figure not shown]
GOALS (Global Operative Assessment of Laparoscopic Skills). The assessed parameters and the scoring system are shown.

Secondary objectives include assessing Non-Technical Skills for Surgeons (NOTSS) score, participant satisfaction, and feasibility outcomes. Table 1 presents the NOTSS score, including their parameters and scoring system, and Figure 2 presents the scoring systems used to obtain satisfaction scores from the involved mentees and mentors in both the intervention and control arms.

**Table 1. T1:** The NOTSS (Non-Technical Skills for Surgeons) score.

Category and elements	Rating^a^
Situation awareness	
Gathering information	1, 2, 3, 4
Understanding information	1, 2, 3, 4
Projecting and anticipating future state	1, 2, 3, 4
Decision-making	
Considering options	1, 2, 3, 4
Selecting and communicating options	1, 2, 3, 4
Implementing and reviewing decisions	1, 2, 3, 4
Communication and teamwork	
Exchanging information	1, 2, 3, 4
Establishing shared understanding	1, 2, 3, 4
Coordinating team activities	1, 2, 3, 4
Leadership	
Setting and maintaining standards	1, 2, 3, 4
Supporting others	1, 2, 3, 4
Coping with pressure	1, 2, 3, 4

a 1: poor, 2: marginal, 3: acceptable, 4: good.

This pilot study will specifically (1) evaluate the feasibility of recruitment, randomization, and intervention delivery; (2) assess the acceptability of the telementoring system among residents and mentors; (3) identify logistical challenges requiring modification before a definitive RCT; and (4) provide preliminary effect size estimates to refine sample size calculations for a future full-scale trial.

**Figure 2. F2:**
[figure not shown]
Resident and mentor satisfaction survey to obtain satisfaction scores from both the intervention and control arms of the study. The satisfaction survey used a 5-point Likert scale, with 1=strong disagreement and 5=strong agreement.

## Methods

### Study Design and Setting

This study is a parallel, 2-group, assessor-blind, multicenter pilot RCT. Participating surgical residents are allocated in a 1:1 ratio to either the intervention group, which receives real-time intraoperative telementoring and postoperative coaching, or the control group, which receives traditional intraoperative mentoring. The intention-to-treat principle will be applied. The study adheres to the latest SPIRIT (Standard Protocol Items: Recommendations for Interventional Trials) 2025 statements recommended for RCT protocols, as shown in Checklist 1 [26].

The Northern Norwegian Health Care Trust comprises 11 hospitals, including 1 university hospital and 10 local hospitals. Four hospitals within the Northern Norwegian Health Care Trust were initially assessed for eligibility as study sites: Sandnessjøen, Mo i Rana, Stokmarknes, and Bodø. Following a feasibility assessment, 2 hospitals—Sandnessjøen and Mo i Rana—were selected as active study sites based on surgical volume, resident availability, geographic location for ease of patient and resident inclusion in the study, and telementoring infrastructure, including the availability of telementors and on-site mentors. Stokmarknes and Bodø were not included as active recruitment sites due to anticipated pressure from acute cases in these locations, which would affect the elective surgical plan that the telementoring project was part of. Additionally, one of the initially included telementors based in Stokmarknes had to withdraw from the study. Although the telementoring infrastructure was initially installed at these locations to support patient and resident inclusion in the study, we ultimately decided to restrict inclusion facilities to Mo i Rana and Sandnessjøen. This facilitated optimal collaboration among actively participating telementors, residents, and the project administrator, KB, who was located in Bodø. Depending on the results of this pilot study, the expansion to include Stokmarknes and Bodø in a definitive RCT will be considered.

For this pilot RCT, 2 of the local hospitals, Sandnessjøen and Mo i Rana, served as study sites. Both locations offer surgical residency training programs that provide LC training.

### Technical Setup of the Telementoring System

Both hospitals, including patients in the study, have implemented ST systems in the ORs. The Olympus telecollaboration platform, MedPresence, provides a telementoring system that uses voice instructions delivered via headphones to assist the mentee throughout laparoscopic surgery. Simultaneously, the telementor observes the procedure in real time via a live stream from the laparoscopic camera. Telestration may be used, at the request of the telementor or the telementee, to provide annotations on a static picture of the ongoing surgical procedure. The telestration session begins when the telementor instructs the mentee to cease surgery and directs their attention to the visual aspect. Telementors may demonstrate surgical planes and strategize dissection.

The telementor may alternate between the external camera, which provides an overview of the laparoscopic trocars and the spatial positions of the OR and anesthesia nurse, and the laparoscopic camera. The system captures audio from the mentor-mentee dialog and footage from the laparoscopic surgery and the external camera. The external camera and its audio recording provide a foundation for assessing interactions between the telementee and OR staff, enabling the evaluation of the telementee’s nontechnical skills.

In both study arms, the standard operative team includes the operating resident, a camera-holding assistant (assisting surgeon), a scrub nurse, and a circulating nurse.

In the intervention group, the local assisting surgeon, an experienced laparoscopic surgeon, holds the laparoscopic camera and assists the operating resident solely by moving the camera to meet the resident’s demands, providing instructional guidance only when patient safety requires it. The camera-holding surgeon’s role is limited to emergency assistance. In the control arm, the on-site mentor, an experienced laparoscopic surgeon, is scrubbed and provides active instruction throughout the procedure, while the same support personnel configuration is maintained in the OR. Figure 3 shows the intraoperative setup during a telementored procedure in the intervention arm.

In the control arm, the Lapco principles of intraoperative communication and the GROW model are not applied during the mentor’s preoperative, intraoperative, and postoperative guidance of the mentee.

**Figure 3. F3:**
[figure not shown]
Configuration of the operating room (OR) setup during telementored sessions in the intervention group. Participating personnel include a resident, a camera-holding surgeon, a scrub nurse, a telementor (remotely located), an anesthesia nurse, and an anesthesiologist. Note the small microphone placed beside the soundbar, beneath the screens displaying the laparoscopic camera images.

### Eligibility Criteria: Residents, Mentors, and Patients

#### Residents

The eligibility criteria for the residents are as follows:

General surgery residents in years 1 to 6 of their specialty education who have partially or completely performed more than 10 laparoscopic proceduresStratification according to experienceHaving completed the mandatory national course on general laparoscopic principles and the mandatory LC courseAgreement with the mentor on the communication model during surgery. This model is derived from the LapcoNor principles [17]. Residents in the intervention group received an introduction to communication principles during telementoring and an orientation to the telementoring equipment used in the OR.

#### Mentors

The eligibility criteria for the mentors are as follows:

Consultant surgeon with more than 5 years of experience performing LCs independentlyAcquainted with the assessment of videos for the GOALS score [27]Both telementors and on-site mentors had to attend the national LapcoNor TT course and follow standardized communication norms with the mentee during surgical mentoring, thus diminishing the bias of communicative difference.

#### Patients

The eligibility criteria for the patients are as follows:

Gallstone disease without a clinical history of cholecystitisBMI <38No previous history of upper abdominal laparotomyNo previous history of percutaneous gallbladder drainagePatient provided informed consent

Each telementoring procedure will be followed by a coaching session in which the mentee describes their performance (an opportunity for self-reflection). The telementor will provide performance-enhancing feedback to formulate a take-home message. Both the GROW model and the Lapco TT model will be used in telementoring sessions as macro- and micromodels for surgical guidance.

Residents will continue their standard surgical training during the study period. No restrictions will be imposed on other educational activities (eg, simulation training and courses). To promote participant retention, procedures will be scheduled within a 3-day block to minimize scheduling conflicts. Residents who cannot complete all 5 procedures will be followed for available outcomes. Reasons for withdrawal will be documented.

### Recruitment Procedures

The residents will be randomized into 2 groups. Residents in the control group will receive traditional OR supervision throughout all 5 consecutive procedures, with on-site mentoring by an experienced surgeon. The intervention group will receive guidance from a remotely located expert via live stream during 5 consecutive procedures.

Recruitment of research participants (surgical residents) will primarily occur at their local hospitals. During 2024 and 2025, all patients referred to hospital surgical departments with a diagnosis of gallstone disease and scheduled for LC will be assessed for inclusion. Study residents will be scheduled for 5 LCs within 3 days. If not enough residents are recruited at the local hospitals, recruitment efforts will be extended to include residents from other hospitals.

### Allocation and Blinding

The randomization process will use a predetermined statistical sequence generated by an external researcher who was not directly engaged in the study. The allocation sequence will be concealed using a centralized web-based randomization system. Personnel enrolling participants will not have access to the sequence until after enrollment. All individuals who actively participate in the experiment will be granted access to the allocation codes after randomization. Residents are enrolled by KB. After enrollment confirmation, the allocation is revealed by KB.

Computer-generated stratification will be used for randomization to create balanced and unpredictable groups. To ensure balance across groups with respect to significant confounders, the randomization process will be stratified by trainees’ experience, explicitly distinguishing between those who had performed 5 to 10 LCs and those who had performed 10 to 20.

### Participant Timeline

To ensure transparency and adherence to reporting standards for RCTs, according to the Consolidated Standards of Reporting Trials (CONSORT), the trial design is summarized in the CONSORT flowchart in Figure 4. The timeline of surgical residents’ inclusion in both groups is shown. Residents who consented to inclusion will be informed of randomization 1 week before the planned procedures. In addition to the planned stepwise procedure description, standardized information on communication during the telementoring procedure will be provided.

This protocol follows the SPIRIT 2025 guidelines for clinical trial protocols. A complete SPIRIT checklist is provided as Checklist 1.

**Figure 4. F4:**
[figure not shown]
Design of the SURGTEACH (Surgical Telementoring in Acquisition of Surgical Skills of Laparoscopic Cholecystectomy) trial: CONSORT flow and participant timeline. The intention-to-treat (ITT) principle will be applied. CONSORT: Consolidated Standards of Reporting Trials; GOALS: Global Operative Assessment of Laparoscopic Skills; NOTSS: Non-Technical Skills for Surgeons.

### Blinding

Blinding the trainees is not feasible given the characteristics of the intervention. Nevertheless, the evaluators who assessed performance needed to be unaware of the assignment of individuals to specific groups. Given the nature of the intervention, unblinding is not applicable to participants. For outcome assessors, any unintentional unblinding would be documented. No emergency unblinding procedures are required because the intervention poses no direct safety risk.

### Interventions

A skilled surgeon will serve as the camera-holding assistant for all procedures in the intervention group. They will intervene only at the time of unexpected events during surgery requiring emergency on-site assistance. Second, residents in the intervention group will receive postoperative coaching grounded in Lapco TT principles and the GROW model. In contrast, the control group will follow standard, unstructured guidance during the procedure. The mentors and mentees will sign a contract accepting the educational setting and the prerequisites before participating in the trial. Table 2 summarizes the intervention and control conditions.

**Table 2. T2:** Comparison of intervention and control groups.

Component	Telementoring group (intervention)	Traditional training group (control)
Mentor location	Remote via secure video link. May use a laptop or other mobile devices	Physically present in operating room
Verbal communication mode	Headphones with a mic during surgery for real-time mentor-mentee communication	Direct verbal communication; physical gestures
Visual guidance	Live stream of procedure. Possibility for static image annotation (telestration); verbal description of dissection planes	Direct pointing; hands-on demonstration capability
Mentor’s view	Laparoscopic camera feed + external OR^a^ camera.	Direct laparoscopic monitor view + peripheral vision of OR
Physical intervention	Not possible (local consultant available for emergencies)	Can take instruments to demonstrate; tactile guidance
Postoperative coaching	Mandatory structured GROW^b^ model session (15‐20 min)	Standard informal feedback (unstructured, variable).
Documentation	All sessions recorded; coaching documented	Standard operative notes only.

a OR: operating room.

b GROW: goals, reality, options, wrap-up.

### Intervention Group (Telementoring)

The telementoring protocol comprises 3 main phases: preprocedural setup and coaching, intraoperative telementoring, and postoperative coaching.

#### Preprocedure Setup and Coaching

Before commencing the surgical procedure, a standardized setup phase of approximately 10 to 15 minutes is implemented. Key steps to ensure operational readiness include the following: the resident confirms connectivity to the telementoring system with the remote mentor; a bilateral communication check of the audio headset is performed, and the video feeds from both the laparoscopic and external OR cameras are verified by the telementor. This phase concludes with a brief preoperative discussion to review the surgical plan and anticipate potential challenges.

#### Intraoperative Telementoring

During the operation, the telementor provides real-time guidance by observing a high-definition video stream and maintaining continuous audio communication via a wireless headset. When anatomical clarification is required, the telementor activates the telestration mode. This process involves the following:

The procedure is temporarily paused using a specific “stop word” command from the mentor.A static image is captured from the laparoscopic feed.The mentor annotates the image using lines, circles, or arrows to highlight relevant anatomical structures, dissection planes, or areas of concern.The resident confirms their understanding of the annotations before the procedure is resumed.

The Lapco communication protocol, an integral component of the Lapco standardized teaching framework, follows the “6 steps”: stop → identify → explain → instruct → check → assess. The steps are defined as follows:

Stop. The telementor (trainer) initiates the sequence by pausing the procedure completely with the stop signal, often when the telementee (trainee) encounters difficulty or reaches a critical juncture, to gain the telementee’s full attention and prevent errors.Identify. The telementor asks the telementee to clearly identify the specific problem, concern, or relevant anatomical structure to ensure mutual understanding of the issue.Explain. The telementor provides a brief explanation of the underlying principle or rationale behind the next required action, connecting theory to practice.Instruct. Clear, concise instructions are provided to the telementee on how to perform the next step correctly.Check. The telementee verbally confirms that they understand the instructions and are prepared to execute them safely by repeating the instructions provided in step 4.Assess: After the telementee attempts the maneuver, the telementor provides an assessment and determines whether the procedure can proceed safely without further instructions or whether the on-site surgeon should assume control of the procedure. The latter should be avoided to maximize learning.

A local consultant surgeon is scrubbed for all procedures and assists as the camera-holding surgeon during the laparoscopic procedure but does not provide teaching input unless patient safety requires intervention.

#### Postoperative Coaching (10-15 Minutes Within 1 Hour of Procedure Completion):

A structured coaching session is conducted postoperatively, within 1 hour of procedure completion, and lasts approximately 10 to 15 minutes. This session uses the GROW model and is conducted via a videoconferencing platform.

The process begins with the resident completing a self-assessment of their performance, focusing on their initial goals and the actual surgical outcomes (goals and reality). Subsequently, the mentor provides constructive feedback, referencing specific procedural moments observed during the operation. The session concludes with the joint identification of specific action points for improvement (options and wrap-up). Finally, the key learning points generated during the session are formally documented for future reference and to support the continuity of training.

### Control Group (Traditional Training)

The control group operates within the framework of conventional surgical training protocols, characterized by direct, in-person mentorship.

#### Intraoperative Mentoring

During the surgical procedure, an experienced consultant surgeon is physically scrubbed in alongside the resident. The primary mode of instruction is direct verbal guidance throughout the operation. Mentors retain discretion to physically interact during the case. They may guide the resident’s hands, indicate anatomical structures on the surgical screen, or temporarily assume control of instruments to demonstrate a specific technique. While the same standardized procedural steps are typically followed, the mentor provides teaching and feedback at their discretion, in the absence of a formalized, structured teaching framework.

#### Postoperative Feedback

Postoperative feedback in this group consists of a standard informal debriefing, conducted solely at the mentor’s discretion. This approach is defined by the absence of mandated structure, specific timing requirements, or formal documentation requirements. This methodology represents the current standard practice in many surgical training environments.

### The Surgical Procedure

The LC procedure was standardized using a stepwise approach, incorporating the principles of creating the critical view of safety before transecting any structure in Calot triangle [28,29]. All included residents were instructed in intraoperative communication in accordance with Lapco and GROW principles. A step-by-step procedure was provided for both mentees and mentors, and adherence was required. A detailed description of the step-by-step surgical procedure is provided in Multimedia Appendix 3.

### Outcomes

#### Primary Outcomes

The primary outcomes are the GOALS and NOTSS scores (Figures 1 and 2). The GOALS score is the only global rating scale developed and validated for assessing laparoscopic surgery. Five subscales are assessed: depth perception, bimanual dexterity, efficiency, tissue handling, and autonomy. Each subscale is scored from 1 to 5, yielding a maximum score of 25 when assessing the resident’s laparoscopic technical skills. The NOTSS score assesses the operating surgeon’s nontechnical surgical skills by evaluating defined parameters [30].

The NOTSS score will be derived from video recordings of interactions between the operating telementee and the rest of the OR team. A 3-member evaluation group of specialized OR nurses will be established to assess the NOTSS score for each procedure by reviewing video footage from the room camera.

The GOALS score will be assessed by video recording the laparoscopic camera footage of each procedure performed by the included registrars. A 3-member evaluation group of expert laparoscopic surgeons will be established to assess the GOALS score for each procedure by reviewing the laparoscopic video footage, including the verbal communication between the mentee and the mentor.

Both evaluation groups will be presented with video footage of each included mentee in a random order to obtain blinded evaluations of the GOALS and NOTSS scores.

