### Data Collection and Management

Each video recording will be stored in the OR recording system. The video recordings will be edited by KB (corresponding author) into predefined segments of the surgical procedure, as specified in the stepwise procedure description. The edited video recordings will be annotated. These standardized, edited recordings will be anonymized and randomized for each resident and distributed to the evaluation group for assessment of GOALS and NOTSS scores.

The project secretary will provide each evaluation group with a Questback questionnaire to collect their assessments. The project secretary, who holds the anonymization and randomization key, will then collect and decode the assessments.

Data will be collected and managed using REDCap, hosted at the University Hospital of Northern Norway [33]. Data items (resident satisfaction and mentor satisfaction) will be collected immediately after each procedure. Given the pilot nature of this study, no formal steering committee or data safety monitoring board was established.

GOALS and NOTSS scores will be collected by giving the mentor group 1 month to assess the video records. Patient-related data will be collected retrospectively by reviewing the electronic health record. The timeline of data collection is shown in Figure 5.

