### Strengths and Limitations

#### Strengths

This study represents the first randomized comparison of telementoring versus traditional training with a primary focus on educational outcomes. It employs validated, objective assessment tools, including GOALS and NOTSS, to ensure robust measurement of both technical and nontechnical skills. Outcome assessment is blinded through standardized video review, reducing the risk of assessor bias. Both study arms use a standardized communication framework, which minimizes variability in mentor–trainee interaction. In addition, postoperative coaching is delivered in a structured manner using the evidence-based GROW model. Randomization is stratified by trainee experience level, further strengthening internal validity and group comparability.

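### The trial is called assessor-blind, but GOALS raters hear the mentor-mentee dialogue and NOTSS raters watch the room camera, so the arm is likely to show; who rates is also stated inconsistently

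*Protocol article*

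**What the plan says.** Study Design and Setting describes a "parallel, 2-group, assessor-blind, multicenter pilot RCT". The Blinding section says that "the evaluators who assessed performance needed to be unaware of the assignment of individuals to specific groups", and Strengths states: "Outcome assessment is blinded through standardized video review, reducing the risk of assessor bias". Limitations mentions only that participants cannot be blinded.

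Primary Outcomes sets out what the raters receive. Three expert laparoscopic surgeons score GOALS "by reviewing the laparoscopic video footage, including the verbal communication between the mentee and the mentor". Three operating room nurses are "to assess the NOTSS score for each procedure by reviewing video footage from the room camera". Clips are shown in random order. Data Collection and Management adds that recordings are cut into predefined segments and anonymized, that they go to the evaluation group, and that the project secretary holds the key. The same section then says: "GOALS and NOTSS scores will be collected by giving the mentor group 1 month to assess the video records".

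**The concern.** GOALS and NOTSS are subjective ratings, and the residents know their arm. Masked rating is therefore the main protection against bias in both outcomes. If raters can tell the arm from the material they are sent, that protection is weakened, and the final report would claim a property that its own methods contradict.

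The pilot status does not remove the problem. Statistical Analysis uses Cohen d from this trial to inform the size of the definitive trial, so any rater lean between arms would be carried forward into that calculation.

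**Working it through.** No figure in the plan needs reproducing. The check sets the sections side by side.

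**1. Arm cues in the GOALS material (stated).** Table 2 and Intraoperative Telementoring give the intervention arm a remote mentor on a headset, a stop word, pauses for annotation of a still image, and a six-step verbal sequence. Technical Setup, Table 2 and the control-arm Intraoperative Mentoring section give the control arm a scrubbed mentor who teaches directly, points, and may "temporarily assume control of instruments to demonstrate a specific technique". The raters are sent the sound of exactly this exchange.

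**2. Arm cues in the NOTSS material (inferred).** Technical Setup says the external camera shows the trocars and staff positions and carries audio. It also says that the intervention camera holder gives guidance only when safety requires it, while the control mentor is scrubbed and instructs throughout. A headset on the resident, or a teaching mentor at the table, would probably be apparent.

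**3. What the safeguards reach.**

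| Stated safeguard | Hides identity | Hides arm |
|---|---|---|
| Random order of clips | helps | no |
| Anonymization, key held by the secretary | yes | no |
| Cutting to predefined segments | no | not stated |
| Documenting unintentional unblinding | no | no; it records the event afterwards |

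No section describes masking the sound, the headset or the mentor. Keeping the dialogue is a stated choice, so this is not a detail left to a fuller document.

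**4. Who rates.** Primary Outcomes names two separate 3-member panels. Data Collection and Management says evaluation group when it describes distribution and questionnaires, then mentor group when it gives the scoring window. Nothing shown bars trial mentors from the panels, and the mentor eligibility criteria require familiarity with GOALS video assessment.

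**5. How much of GOALS can be masked.** There are five items scored 1 to 5, with a maximum of 25. Depth perception, bimanual dexterity, efficiency and tissue handling can be judged from silent laparoscopic video: 4 × 5 = 20 points. Autonomy, 1 × 5 = 5 points, may need the dialogue.

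**6. How a lean would enter the result.** If raters favoured one arm by b points, the observed mean difference would be the true difference plus b. With the plan's SD of 2.5, Cohen d would shift by b / 2.5, which is 1 / 2.5 = 0.4 per point. The document gives no value or sign for b.

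**The case against.** Several counter-arguments have force.

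- **The mentor group is probably a slip.** A reader might infer that mentors score their own trainees. The documents do not support that. The same section otherwise says evaluation group, and NOTSS goes to nurses, who cannot be the consultant surgeons who mentor. The wording must be reconciled, but it is not evidence of self-rating.
- **The dialogue contrast is not cleanly stated.** The mentor eligibility criteria, The Surgical Procedure and Strengths say that both arms share communication standards or instruction. Technical Setup, Table 2 and the control-group sections say that control teaching is unstructured. Even if the shared framework applies, the remote voice and any stop word or telestration pause remain cues. Telestration is optional, so not every clip need contain one.
- **The NOTSS part is inference.** No section describes control-arm room footage, Table 2 lists only operative notes as control documentation, and both arms have a camera-holding assistant. The inference is strong but remains an inference.
- **Blinding is not shown to be wholly lost.** Order, anonymization and segmenting offer some protection, and the segment definitions are in an appendix that is not shown. A reader might also infer that footage of a mentor operating is certainly scored as the resident's work. That cannot be said without the appendix.
- **This is a pilot.** The plan emphasises effect sizes and CIs and disclaims definitive conclusions. That limits the consequence of a false positive, but not the effect of bias on the estimate itself.

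**Conclusion.** The concern holds in this form: the assessor-blind label conflicts with the material the raters are given. For GOALS the conflict rests on explicit text, and for NOTSS on a strong inference. The stated safeguards mask identity rather than arm, and the description of who rates is inconsistent.

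The size and direction of any bias cannot be estimated from the document. A reader might want to turn it into a false-positive rate. For example, with no true effect, SD 2.5 and 5 residents per arm, an assumed lean of 1.0 to 2.5 points towards telementoring would raise the chance of a significant result in its favour from 2.5% to 8.1% to 28.6%. The arithmetic is right, but nothing in the document supports that lean or its sign. The Discussion itself says that intuition favours a mentor who is physically present, so raters could lean the other way. The conclusion does not depend on these figures.

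**What to change.** 1. Have GOALS raters score and lock depth perception, bimanual dexterity, efficiency and tissue handling on muted laparoscopic clips. Release the audio afterwards for autonomy only. Report the 4-item masked score (range 4 to 20) beside the 25-point total.
2. Flag segments where someone other than the resident operates, so that the motor items are rated on the resident's own work. Keep those segments available for the autonomy rating. Deleting them would remove takeover evidence mainly from the control arm and could inflate its autonomy scores.
3. Replace the mentor group with the evaluation groups, and bar anyone who mentored or assisted in the trial from rating.
4. Record each rater's guess of the arm for every clip. For GOALS, take it after the motor items are locked and before the audio is released. Muted clips may still carry cues such as pauses or flagged takeovers, and the guesses show how well the masking worked.
5. Describe NOTSS and autonomy as not reliably blinded, correct Study Design and Setting and Strengths accordingly, and add the point to Limitations.

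The cost is some extra editing, two questionnaire fields (the arm guess and the lock), and re-rating of any clips already scored with sound. The document does not say whether any have been. Recruitment Status reports 5 + 3 = 8 residents included by December 2025. If each completed five procedures, at most 8 × 5 = 40 procedures, or 40 × 3 = 120 individual GOALS ratings, would need repeating. Raters who have already heard the audio would not be fully masked on a second viewing, so the change is best made before scoring begins.
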